### 1.3 Current research questions and research hypotheses

#### 1.3.1 Intensive antiplatelet therapy in patients with acute ischemic stroke or high-risk TIA from atherosclerosis

The INSPIRES study, in which patients with acute ischemic stroke or high-risk TIA from atherosclerosis were treated with antiplatelet therapy was conducted to answer the questions unsolved in the CHANCE study:

##### 1) Whether patients with ischemic stroke from atherosclerosis with higher NIHSS scores may benefit from DAPT?

The CLAIR study expanded the NIHSS score of enrolled patients to 8, and the result showed no increased risk of bleeding after DAPT. The SOCRATES trial expanded the enrolled population NIHSS score to 5. Therefore, patients with high NIHSS score may benefit from DAPT. **The INSPIRES trial**

enrolled patients with expanded NIHSS score to 5.

**2) Whether patients with ischemic stroke from atherosclerosis with extended time windows of onset may benefit from DAPT?**

Meta-analysis published in 2013 showed that ischemic stroke patients enrolled within 72 hours of onset benefit from DAPT. **Therefore, the INSPIRES trial expands the time window of onset to 72 hours.**

**3) Whether ischemic stroke with mild stenosis but multiple infarcts may benefit from DAPT?**

The CHANCE imaging subgroup analysis showed that patients with multiple infarcts significantly benefited from DAPT, rather than patients with minor stroke with single infarction and TIA. Therefore, **multiple infarctions from embolization may be an important target for DAPT.**

The results of the pooled analysis of the CHANCE and the POINT trials suggested that DAPT with aspirin and clopidogrel initiated within 24 hours of onset in patients with noncardiogenic minor ischemic stroke (NIHSS score  $\leq 3$ ) or high-risk TIA (ABCD score  $\geq 4$ ) significantly reduced the incidence of major ischemic events relative to aspirin alone, which was also cited by the 2019 American Heart Association/ American Stroke Association Guidelines for the Early Management of Acute Ischemic Stroke as a class A evidence recommendation. Therefore, patients with non-cardiogenic mild ischemic stroke (NIHSS score  $\leq 3$ ) or high-risk TIA (ABCD score  $\geq 4$ ) within 24 hours of onset were not included in this study.

**1.3.2 Intensive lipid-lowering therapy in patients with acute ischemic stroke or high-risk TIA from atherosclerosis**

The SPARCL study did not answer the question of the efficacy and safety of statin therapy for ischemic cerebrovascular disease in the acute phase, because it enrolled patients with ischemic stroke and TIA within 6 months of onset, with a mean time of 87 days. It remains unclear for immediate intensive statin therapy to reduce the early recurrence risk in patients with ischemic stroke from large-artery atherosclerosis.

Moreover, atorvastatin at doses of 40mg/d and 80mg/d are both recommended as intensive statin treatment in the 2018 American Heart Association/ American Stroke Association Guidelines for the Early Management of Patients with Acute Ischemic Stroke. However, the difference between the two doses in terms of therapeutic effect has not been observed in Asian patients. Some studies have shown that statin intolerance varies in race. Compared with Western populations, Chinese have higher incidence of intensive statin intolerance, which makes it difficult for guideline promotion. Therefore, it is necessary to discuss the efficacy and safety of intensive statin treatment with different doses of atorvastatin in acute phase of ischemic stroke. Meanwhile, 2018 American Heart Association/ American Stroke Association Guidelines for the Early Management of Patients with Acute Ischemic Stroke show that high-intensity statin therapy should be given in the acute phase for patients with TIA and ischemic stroke, but there is a lack of evidence on when to initiate the statin therapy. The ASSORT study explored the efficacy and safety of delayed statins, but due to its small sample size, it was not used as evidence

for guideline recommendations . Hence, it is necessary to discuss the efficacy and safety of immediate or delay intensive statin treatment in reducing stroke recurrence and improving functional outcomes.

Based on the above evidence, we made the following 3 hypotheses: in patients with acute ischemic stroke or TIA with high-risk symptomatic intracranial or extracranial atherosclerosis, ① Intensive antiplatelet therapy reduces the risk of stroke recurrence at 90 days without increasing the risk of bleeding compared with standard antiplatelet therapy; ② Immediate intensive statin therapy (atorvastatin 80mg/d) reduces the risk of stroke at 90 days compared with delayed intensive statin therapy (atorvastatin 40mg/d); ③ Intensive antiplatelet therapy combined with immediate intensive statin therapy (atorvastatin 80mg/d) reduces the risk of stroke at 90 days compared with standard antiplatelet therapy combined with delayed intensive statin therapy (atorvastatin 40mg/d).

Therefore, a randomized, double-blind, placebo-controlled, multicenter, 2\*2 factorial design trial was conducted to evaluate the efficacy and safety of intensive antiplatelet therapy versus standard antiplatelet therapy in reducing the risk of new stroke at 90 days in acute mild ischemic stroke or high-risk TIA patients attributed to intracranial or extracranial arterial atherosclerosis; to evaluate the efficacy and safety of immediate intensive statin therapy versus delayed intensive statin therapy in reducing the risk of stroke at 90 days in acute mild ischemic stroke or high-risk TIA patients attributed to intracranial or extracranial arterial atherosclerosis; To evaluate the effectiveness of intensive antiplatelet therapy combined with immediate intensive statin therapy versus standard antiplatelet therapy combined with delayed intensive statin therapy in reducing the risk of stroke at 90 days in acute mild ischemic stroke or high-risk TIA patients attributed to intracranial or extracranial arterial atherosclerosis.

## 2. Study Purposes

### 2.1 Primary purposes:

**2.1.1** To evaluate the efficacy and safety of intensive antiplatelet therapy versus standard antiplatelet therapy in reducing the risk of new stroke at 90 days in acute mild ischemic stroke or high-risk TIA patients attributed to extracranial or intracranial atherosclerosis.

**2.1.2** To evaluate the efficacy and safety of immediate intensive statin therapy (atorvastatin 80mg/d) versus delayed intensive statin therapy (atorvastatin 40mg/d) in reducing the risk of new stroke at 90 days in acute mild ischemic stroke or high-risk TIA patients attributed to extracranial or intracranial atherosclerosis.

**2.1.3** To evaluate the efficacy and safety of intensive antiplatelet combined with immediate intensive statin therapy (atorvastatin 80mg/d) versus standard antiplatelet combined with delayed intensive statin therapy (atorvastatin 40mg/d) in reducing the risk of new stroke at 90 days in acute mild ischemic stroke or high-risk TIA patients attributed to extracranial or intracranial atherosclerosis.

### Notes:

- Intensive antiplatelet therapy refers to dual antiplatelet therapy with aspirin and clopidogrel;
- Standard antiplatelet therapy refers to antiplatelet monotherapy with aspirin;
- Immediate intensive statin therapy (atorvastatin 80mg/d) refers to lipid-lowering therapy from the onset with atorvastatin at a dose of 80 mg daily and last for the first 21 days, followed by 40 mg daily for days 22-90;
- Delayed intensive statin therapy (atorvastatin 40mg/d) refers to lipid-lowering therapy with atorvastatin at a dose of 40 mg for days 4-90);
- Acute mild ischemic stroke or high-risk TIA patients attributed to extracranial or intracranial atherosclerosis: at least one of the following characteristics:
  - a) Mild ischemic stroke (NIHSS score 4–5) within 24 hours after onset and either of the following imaging characteristics:
    - 1) Acute single infarction with  $\geq 50\%$  stenosis of a major intracranial or extracranial artery that likely accounts for the infarction and clinical presentation.
    - 2) Acute multiple infarctions documented by head CT or MRI, attributed to large-artery atherosclerosis, including non-stenotic vulnerable plaques.
  - b) Mild ischemic stroke (NIHSS score  $\leq 5$ ) or high-risk TIA (ABCD score  $\geq 4$ ) within 24-72 hours after onset and meet any of the following imaging characteristics:
    - 1) TIA with  $\geq 50\%$  stenosis of a major intracranial or extracranial artery that likely accounts for the clinical presentation.
    - 2) Acute single infarction with  $\geq 50\%$  stenosis of a major intracranial or extracranial artery that likely accounts for the infarction and clinical presentation.
    - 3) Acute multiple infarctions documented by head CT or MRI, attributed to large-artery atherosclerosis, including non-stenotic vulnerable plaques.

### 2.2 Secondary purposes:

**2.2.1** To evaluate the efficacy of intensive antiplatelet therapy versus standard antiplatelet therapy, immediate intensive statin therapy (atorvastatin 80mg/d) versus delayed intensive statin therapy

(atorvastatin 40mg/d), intensive antiplatelet therapy combined with immediate intensive statin therapy (atorvastatin 80mg/d) versus standard antiplatelet therapy combined with delayed intensive statin therapy respectively (atorvastatin 40mg/d) at 90 days in acute mild ischemic stroke or high-risk TIA patients attributed to intracranial or extracranial atherosclerosis on the incidence of (definitions shown in appendix 1, 2 and 5):

- Combined vascular events: stroke (ischemic or hemorrhagic), myocardial infarction, and cardiovascular death.
- Ischemic stroke
- TIA
- Severity of stroke or TIA on an ordinal scale: a six-level ordered category scale combined vascular events with mRS score at 90 days: fatal stroke (stroke with subsequent death), severe stroke (stroke followed by mRS of 4-5), moderate stroke (stroke followed by mRS of 2-3), mild stroke (stroke followed by mRS of 0-1), TIA, and no stroke/TIA
- Myocardial infarction
- Vascular death
- All-cause death
- Poor functional outcome (mRS score 2-6)
- Poor quality of life (EQ-5D scale index score  $\leq 0.5$ )

**2.2.2** To evaluate the efficacy in decreasing early neurological deficits (increase in NIHSS score at 7days), stroke recurrence, all-cause mortality and poor functional outcome (mRS score 2-6) at 1 year of intensive antiplatelet therapy versus standard antiplatelet therapy, immediate intensive statin therapy (atorvastatin 80mg/d) versus delayed intensive statin therapy (atorvastatin 40mg/d), intensive antiplatelet therapy combined with immediate intensive statin therapy (atorvastatin 80mg/d) versus standard antiplatelet therapy combined with delayed intensive statin therapy (atorvastatin 40mg/d) respectively in acute mild ischemic stroke or high-risk TIA patients attributed to intracranial or extracranial atherosclerosis. The new stroke or TIA is classified on a six-level ordered category scale combined vascular events with mRS score at 1 year: fatal stroke (stroke with subsequent death), severe stroke (stroke followed by mRS of 4-5), moderate stroke (stroke followed by mRS of 2-3), mild stroke (stroke followed by mRS of 0-1), TIA, and no stroke/TIA.

## 2.3 Safety purposes

**2.3.1** To evaluate safety of intensive antiplatelet therapy versus standard antiplatelet therapy for 90 days in acute mild ischemic stroke or high-risk TIA patients attributed to intracranial or extracranial atherosclerosis on the incidence of:

- Moderate to severe bleeding (Appendix 6)
- Intracranial hemorrhage
- Hepatotoxicity: Alanine aminotransferase (ALT) or Aspartate aminotransferase (AST) > 3 times the upper limit of normal value.

- Muscle toxicity: Creatine kinase (CK) > 10 times the upper limit of normal value, or the presence of muscle pain, myopathy, or rhabdomyolysis.
- Death
- Other adverse events (AEs) / severe adverse events (SAEs)

**2.3.2** To evaluate safety of immediate intensive statin therapy (atorvastatin 80mg/d) versus delayed intensive statin therapy (atorvastatin 40mg/d) for 90 days in acute mild ischemic stroke or high-risk TIA patients attributed to intracranial or extracranial atherosclerosis on the incidence of:

- Moderate to severe bleeding (Appendix 6)
- Intracranial hemorrhage
- Hepatotoxicity: Alanine aminotransferase (ALT) or Aspartate aminotransferase (AST) > 3 times the upper limit of normal value.
- Muscle toxicity: Creatine kinase (CK) > 10 times the upper limit of normal value, or the presence of muscle pain, myopathy, or rhabdomyolysis.
- Death
- Other AEs / SAEs

**2.3.3** To evaluate the safety of intensive antiplatelet therapy combined with immediate intensive statin therapy (atorvastatin 80mg/d) versus standard antiplatelet therapy combined with delayed intensive statin therapy (atorvastatin 40mg/d) for 90 days in acute mild ischemic stroke or high-risk TIA patients attributed to intracranial or extracranial atherosclerosis on the incidence of:

- Moderate to severe bleeding (Appendix 6)
- Intracranial hemorrhage
- Hepatotoxicity: ALT or AST > 3 times the upper limit of normal value.
- Muscle toxicity: CK > 10 times the upper limit of normal value, or the presence of muscle pain, myopathy, or rhabdomyolysis.
- Death
- Other adverse events / severe adverse events

## 2.4 Subgroup analysis

**2.4.1** To evaluate the efficacy of intensive antiplatelet therapy versus standard antiplatelet therapy, immediate intensive statin therapy (atorvastatin 80mg/d) versus delayed intensive statin therapy (atorvastatin 40mg/d), and intensive antiplatelet combined with immediate intensive statin therapy (atorvastatin 80mg/d) versus standard antiplatelet combined with delayed intensive statin therapy (atorvastatin 40mg/d) in reversing intracranial atherosclerotic artery stenosis and stabilizing the atherosclerotic vulnerable plaque in the high resolution MRI subgroup.

**2.4.2** To evaluate the efficacy of intensive antiplatelet therapy versus standard antiplatelet therapy for 90 days on the incidence of the primary outcome in different subgroups:

- Subjects aged > 65 years vs. those aged ≤65 years.
- Female vs. male patients.

- Those with NIHSS score 4-5 vs. those with NIHSS score  $\leq 3$  at admission.
- Those randomized within 24 hours of onset vs. those randomized between 24 and 72 hours since onset.
- Those with ischemic stroke/TIA related to extracranial artery atherosclerosis vs. those related to intracranial artery atherosclerosis.
- Those with intracranial stenosis vs. those without intracranial stenosis.
- Those with extracranial stenosis vs. those without extracranial stenosis.
- Those with multiple infarctions vs. those with single infarction vs. those without infarction.
- Those with severe stenosis ( $\geq 70\%$ ) vs. those with moderate stenosis (50%-69%).
- Those with hypertension vs. those who are normotensive.
- Diabetic patients vs. nondiabetics.
- Those with dyslipidaemia vs. without dyslipidaemia.
- Those with atherogenic dyslipidaemia (HDL-C $<40$  mg/dL and TG $>200$  mg/dL) vs. without atherogenic dyslipidaemia.
- Those with statin therapy within 1 month before randomization vs. without statin therapy.

In addition, relevant subgroups will be examined for genetic variability and biomarker characteristics.

**2.4.3** To evaluate the efficacy of immediate intensive statin therapy (atorvastatin 80mg/d) versus delayed intensive statin therapy (atorvastatin 40mg/d) for 90 days on the incidence of the primary outcome in subgroups which is the same as those in 2.4.2.

### 3. Study Design

#### 3.1 Study design

- A Randomized, double-blind, placebo-controlled, multicenter, 2×2 factorial trial
- The trial is intended to enroll 6100 subjects and complete follow-up of all subjects within 5 years.
- Centralized, unified and randomized grouping.
- Subjects will be randomly assigned to the following four groups:
  - A:** Intensive antiplatelet therapy +immediate intensive statin therapy (atorvastatin 80mg/d)
  - B:** Intensive antiplatelet therapy +delayed intensive statin therapy (atorvastatin 40mg/d)
  - C:** Standard antiplatelet therapy +immediate intensive statin therapy (atorvastatin 80mg/d)
  - D:** Standard antiplatelet therapy +delayed intensive statin therapy (atorvastatin 40mg/d)

#### Identity of study medication:

| Groups                             | Date after Randomization | Dosage of study medication                      |
|------------------------------------|--------------------------|-------------------------------------------------|
| Intensive antiplatelet therapy     | Day 1                    | Clopidogrel 300mg/ day + aspirin 100-300mg/ day |
|                                    | Day 2 - Day21±2          | Clopidogrel 75mg/ day + aspirin 100mg/ day      |
|                                    | Day22±2 - Day 90         | Clopidogrel 75mg/ day + aspirin placebo         |
| Standard antiplatelet therapy      | Day 1                    | Aspirin 100-300mg/ day + clopidogrel placebo    |
|                                    | Day 2 - Day 90           | Aspirin 100mg/ day + clopidogrel placebo        |
| Immediate intensive statin therapy | Day 1 - Day21±2          | Atorvastatin 80mg/ day                          |
|                                    | Day22±2 - Day 90         | Atorvastatin 40mg/ day                          |
| Delayed intensive statin therapy   | Day 1 - Day3             | Atorvastatin placebo                            |
|                                    | Day 4 - Day21±2          | Atorvastatin 40mg/ day + atorvastatin placebo   |
|                                    | Day22±2 - Day 90         | Atorvastatin 40mg/ day                          |

## Research design (drawing)

[figure not shown]

## 3.2 Follow-up plan

Subjects will receive a face-to-face visit at baseline, Day7±2, Day14 (or hospital discharge) and Day90 ± 7, and a telephone visit at the 12th month±14 days after randomization. In addition, patients will be interviewed when new neurologic symptoms or suspicious events occur, including worsening of index ischemic events, new transient or persistent neurological symptoms.

## 3.3 Study execute time

| Project Work Description                                                 | Estimated Completion Time |
|--------------------------------------------------------------------------|---------------------------|
| Study design, ethical review, study registration, sub-center recruitment | 2018-06                   |
| The project is officially launched and the first subject is enrolled     | 2018-07                   |
| All subjects are enrolled and grouped                                    | 2021-12                   |
| 90-day follow-up are finished for all subjects                           | 2022-03                   |
| Data cleaning and database locking                                       | 2023-03                   |
| Clinical trial report completion                                         | 2023-06                   |
| Results publication                                                      | 2023-12                   |

## 4. Study Outcomes

### 4.1 Primary outcome

Stroke (ischemic or hemorrhagic)

### 4.2 Secondary outcomes:

- Combined vascular events : Stroke (ischemic or hemorrhagic), myocardial infarction, or cardiovascular death
- Ischemic stroke
- TIA
- Severity of stroke or TIA on an ordinal scale: (a six-level ordered category scale combined vascular events with mRS score: fatal stroke (stroke with subsequent death), severe stroke (stroke followed by mRS of 4-5), moderate stroke (stroke followed by mRS of 2-3), mild stroke (stroke followed by mRS of 0-1), TIA, and no stroke/TIA)
- Myocardial infarction
- Vascular death
- All-cause death
- Poor functional outcome (mRS score 2-6)
- Poor quality of life (EQ-5D scale index score  $\leq 0.5$ )
- Early neurological deficits (increase in NIHSS score at 7 days)

### 4.3 Primary safety outcome

- Moderate to severe bleeding (Appendix 6)

### 4.4 Secondary safety outcomes

- Intracranial hemorrhage
- Hepatotoxicity: ALT or AST  $> 3$  times the upper limit of normal value;
- Muscle toxicity: CK  $> 10$  times the upper limit of normal value, or the presence of muscle pain, myopathy, or rhabdomyolysis.
- Death
- Other AEs / SAEs

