## **7. Study Implementation**

### **7.1 Randomization procedures**

Random number lists will be generated by the Statistics and Data Center at the China National Clinical Research Center for Neurological Diseases (Beijing, China). Regimens for patients will be packed according to the random code lists. Patients will be assigned to four groups with the approximate ratio of 1:1:1:1, and receive: A intensive antiplatelet therapy+ immediate intensive statin therapy (atorvastatin 80mg/d), B intensive antiplatelet therapy+ delayed intensive statin therapy (atorvastatin 40mg/d), C standard antiplatelet therapy+ immediate intensive statin therapy (atorvastatin 80mg/d), or D standard antiplatelet therapy+ delayed intensive statin therapy (atorvastatin 40mg/d) respectively. Randomization will be centralized. We applied randomized block design to generate random number to ensure the ratio between the four groups will be approximately 1:1:1:1. If a center runs out of its random code lists, a new block will be placed to the center for new random numbers. Each patient eligible to the INSPIRES trial will be assigned a random number in order strictly and the corresponding study drug box.

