3. Routine blood counts, biochemical panel (including alanine transaminase, aspartate aminotransferase, alkaline phosphatase, creatine kinase, creatine kinase-MB) and coagulation function should be performed on day7 (If the test had been completed within 24 hours of screening or randomization, there was no requirement to review it). Routine blood counts and biochemical panel (including alanine transaminase, aspartate aminotransferase, alkaline phosphatase, creatine kinase, creatine kinase-MB, low-density lipoprotein cholesterol, high-density lipoprotein cholesterol, total cholesterol, triglyceride) should be performed on day  $90 \pm 7$  after randomization to monitor hepatotoxicity and muscle toxicity of statin.
4. Fasting venous blood should be collected within 24 hours of randomization (If not, 72 hours after randomization is the final deadline) and  $90 \pm 7$  days after randomization.
5. High-resolution MRI examinations should be performed for patient enrolled in the subgroup of high-resolution MRI, within 24 hours and 90 days  $\pm 7$  hours after randomization.

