Moderate to severe bleeding, intracranial hemorrhage, and overall mortality will be calculated using the Kaplan-Meier curve to simulate the 3-month cumulative risk, and the Cox proportional hazards model to calculate the HR and 95% confidence interval.

For other adverse events and laboratory abnormalities, the cases which was normal before the treatment and abnormal after the treatment would be mainly analyzed and listed, in order to the comparison of differences before and after treatment.

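### Muscle toxicity counts unqualified muscle pain the same as objective muscle injury, so the two should also be reported separately by arm

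*Supplement*

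**What the plan says.** The Summary, section 2.3 and section 4.4 of protocol version 4.0 use the same definition. Muscle toxicity is CK above 10 times the upper limit of normal, "or the presence of muscle pain, myopathy, or rhabdomyolysis". Muscle pain carries no qualifier of severity, duration, CK level or relation to treatment. Myopathy and rhabdomyolysis are not defined. In the same list, hepatotoxicity is a purely laboratory threshold.

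Safety of immediate versus delayed intensive statin is an objective in its own right (2.3.2). Section 1.3.2 motivates the comparison of the two doses partly by tolerability, stating that "Chinese have higher incidence of intensive statin intolerance" than Western populations.

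On analysis, section 16.3.2.2 gives a time-to-event method to three safety outcomes only: "Moderate to severe bleeding, intracranial hemorrhage, and overall mortality will be calculated using the Kaplan-Meier curve". For other adverse events and laboratory values, cases normal before treatment and "abnormal after the treatment would be mainly analyzed and listed". Section 4.4 also has a residual entry, "Other AEs / SAEs". The notes to table 10.9 schedule CK at day 7 and day 90, the latter "to monitor hepatotoxicity and muscle toxicity of statin". If the day-7 tests had been done within 24 hours of screening or randomization, "there was no requirement to review it".

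**The concern.** One report of muscle pain contributes as much to this outcome as one case of rhabdomyolysis. When a common, unspecific component is joined by a simple or to a rare, specific one, the common component can supply most of the count. If its rate does not depend on treatment, it adds the same number of cases to both arms and pulls the risk ratio towards 1.

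Muscle toxicity and hepatotoxicity are the two statin-specific outcomes in the safety list. A composite with similar totals in both arms could be read as reassurance about muscle injury at 80 mg when it mainly reflects background pain. Conversely, a difference driven by pain alone could be read as muscle injury. The definition by itself does not let the reader tell these cases apart.

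**Working it through.** **Inputs from the documents.** 6100 patients; "Patients will be assigned to four groups with the approximate ratio of 1:1:1:1", hence 3050 per statin arm. Two-sided alpha 0.05. Table 2 uses 2896 evaluable per arm after 5% loss.

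**Assumed inputs.** All muscle-event rates, because the documents give none.

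**Formula.** Normal approximation for two proportions, n per arm:
power = Φ[(|p1 − p2| − 1.96·SE0) / SE1], with SE0 = √(2·p̄(1 − p̄)/n) and SE1 = √((p1(1 − p1) + p2(1 − p2))/n).

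**Check against the plan's own figure.** For stroke, 0.1157 versus 0.0930 with n = 2896 gives 0.8068; Table 2 states 0.807. Reproduced. This validates the formula only; no power is stated for muscle toxicity.

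**Objective injury alone, 0.2% versus 0.8%, n = 3050.** Expected events are 6.1 and 24.4. SE0 = √(2 × 0.005 × 0.995/3050) = 0.001806; SE1 = √((0.001996 + 0.007936)/3050) = 0.001805. Power = Φ[(0.006 − 1.96 × 0.001806)/0.001805] = Φ(1.36) = 0.91.

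**Pooled with pain at the same rate b in both arms.** Pooled risk = 1 − (1 − injury)(1 − b). At b = 1%: 1 − 0.998 × 0.99 = 1.198% and 1 − 0.992 × 0.99 = 1.792%. The risk ratio is 1.50 and power is 0.48. Pain-only share of the control count = (1.198 − 0.2)/1.198 = 83%.

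| Background pain, both arms | Pooled risks | Risk ratio | Pain-only share, control arm | Power |
|---|---|---|---|---|
| 0 | 0.20% v 0.80% | 4.00 | 0 | 91% |
| 1% | 1.20% v 1.79% | 1.50 | 83% | 48% |
| 3% | 3.19% v 3.78% | 1.18 | 94% | 24% |
| 5% | 5.19% v 5.76% | 1.11 | 96% | 16% |
| 10% | 10.18% v 10.72% | 1.05 | 98% | 10% |

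With 2896 per arm, power is 90% alone, 46% at 1% pain and 16% at 5%. A second assumed pair, 0.1% versus 0.5% with 2896 per arm, goes from 0.80 alone to 0.27 at 1% pain and 0.09 at 5%.

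**If pain also rises with the intensive statin, n = 3050.** Objective 0.1% versus 0.4% has 65% power alone. With pain 2% versus 3%, the pooled risks are 2.10% and 3.39% and power is 87%. Objective 0.2% versus 0.8% with the same pain rates goes from 91% to 95%. The direction of the effect on power therefore depends on whether pain is related to treatment.

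**Whether other parts of the plan already separate the components.** The laboratory rule in 16.3.2.2 concerns shifts from normal to abnormal and names no 10-times threshold; Appendix 7 lists no CK criterion. Exclusion 10 removes only CK above 5 times the limit, so a patient can enter with raised CK, later exceed 10 times, and not qualify as normal before treatment. The 80 mg dose runs to day 21±2 and both arms are on 40 mg at day 90, so at most one scheduled post-baseline CK, which can be waived, falls in the period of different doses. These routes record objective events but do not define them as an outcome compared by arm.

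**The case against.** A reader might infer that non-specific pain decides the count, that a real increase in muscle injury would be hidden, and that pain should therefore be removed from the definition. The documents do not support this.

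- No rate of muscle pain, CK rise or myopathy appears anywhere. That pain dominates is plausible over the range shown, but not established.
- Dilution follows from assuming equal pain in both arms. Pain that rises with dose would be a plausible part of intolerance, and then the composite can be the more powerful outcome. A sensitive definition that includes symptoms is a legitimate choice.
- CK is measured on schedule, normal-to-abnormal shifts are analysed and listed, and adverse events are recorded, so objective injury would leave a trace in the data.
- The strict outcome may itself be weak: 65% power at 0.1% versus 0.4%.
- Section 16.3 describes itself as an overview and defers the planned analyses to an analysis plan that is not shown. A component table is commonly left there, so its absence from the protocol is not in itself a fault.

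All of this stands against removing pain and against the claim that injury would be hidden. It does not remove the narrower point: the protocol's own definition merges symptoms and injury, and none of the reporting it describes presents objective injury by arm as a defined outcome.

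**Conclusion.** A minor point that holds as a matter of definition. The composite gives unqualified muscle pain the same weight as CK above 10 times the limit, myopathy or rhabdomyolysis, so on its own it cannot support a conclusion about statin muscle injury in either direction. Under the assumptions that unrelated pain occurs in 1% to 10% of both arms and objective injury in 0.2% versus 0.8%, power falls from about 91% to between 48% and 10%. If pain is related to treatment, power may rise instead, but what the difference represents remains unclear. Both cases argue for showing the components, and neither argues for dropping pain. This is a secondary safety outcome with no named test and no stated power, so no figure in the plan is wrong.

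**What to change.** Keep the composite in the Summary, 2.3 and 4.4 as a summary line. Add, in 4.4 or in the analysis plan before database lock, by-arm reporting of:

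- (a) CK above 10 times the upper limit of normal, myopathy or rhabdomyolysis, with working definitions of the last two;
- (b) muscle pain without any of these.

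State that conclusions about statin muscle injury rest on (a), and that (b) describes symptoms.

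The cost is a sentence of definition and a few table rows, from data already to be recorded; conduct does not change. The downside is that (a) will have few events. For example, 6 versus 24 events in 3050 per arm gives a risk ratio of 4.0. The standard error of its logarithm is √(1/6 + 1/24 − 2/3050) = 0.456, so the 95% interval runs from about 1.6 to 9.8. Report (a) with its interval, and do not read a non-significant result as absence of harm.
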